Studies reported positive clinical effects with the use of tDCS combined with rehabilitation programs. In a meta-analysis (7) tDCS improved PC through the modulation of cortical excitability, which this technique could be a choice to enhance functionality and independence, and thus, reduce the rate of falls in individuals with a balance disorder, mainly on primary motor cortex (M1) stimulation. However, the effects of tDCS on the cerebellar cortex should be better investigated due to divergence in the study results. Are recognized that both early and late blind people have morphological changes in their whole brain, and the cerebellum is one of these structures. For example, Kosif et al. (8) showed a smaller volume of cerebellar area in congenital blindness subjects compared to sighted subjects. But systematic review studies showed positive effects of cerebellar tDCS to modulate cerebellocerebral networks (9, 10). But until the present, no study has investigated the effects of cerebellar tDCS on gait and PC in blind people.

As stated earlier for the visually impaired people, motor control is quite challenged even in simple tasks that require PC due to their blindness, and that tDCS induces cerebellar excitability changes (11), in which can modulate cerebellar-motor cortex excitability and thus, affect positively PC processing (12). The present study hypothesizes that tDCS can potentiate the effects of a proprioceptive exercises on both static and dynamic PC in blind subjects. The secondary objectives are (1) to determine possible differences in PC betweenindividuals with congenital and acquired blindness; (2) to evaluate the motor pattern of gait with and without the use of a guide stick when wearing shoes or while barefoot; and (3) to analyze whether proprioceptive exercises with or without tDCS can lead to different results with regard to PC.

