### Sample Size Estimation

The sample size will be estimated from Phase II where participants will be randomly allocated into four groups (10 each group). Then the calculation will be considering the minimal difference between the mean of an analysis of variance results obtained from both gait speed and the displacement of the center of pressure (COP) as the primary outcome. Thus, the sample size will be estimated with a unidirectional alpha of 0.05 and an 85% statistical power. The sample determined by the calculation will be increased by 20% to compensate for possible dropouts.

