### Statistical Analysis

The data will be analyzed by Shapiro-wilk test to determine adherence to the Gaussian curve. If the parametric distribution is confirmed, the data will be expressed as mean and standard deviation, and for non-parametric variables, data will be expressed as the median and interquartile range. The effect size will be calculated based on the difference between means of the preintervention and post-intervention evaluations and will be expressed with their respective 95% confidence intervals.

An ANOVA or the Kruskal-Wallis test will be used for the analysis of the effects obtained in the phases one and two of the study. The Bonferroni correction for multiple comparisons will be employed as a *post-hoc* test. The analyses will be performed considering spatiotemporal gait variables, variables of COP parameters, and EMG signals as the dependent variables. The fixed independent variables in Phase I will be group (congenital and acquired blindness, and sighted), auxiliary resource (with and without guide stick), and shoes (with and without). In Phase II and III, the dependent variables will be the same as described in phase I, and for the fixed independent variables will be groups plus active and sham tDCS groups, evaluation time (preintervention, post-intervention, and follow-up) and group^*^evaluation time interaction. *P* < 0.05 will be considered indicative of statistical significance. The data will be analyzed using the Statistical Package for the Social Sciences (SPSS v.19.0) and Biostat (Analystsoft v. 2008.5.0.1).

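### Bonferroni on the three-level Phase I group factor is valid but costs about 3 to 18 points of power on congenital versus acquired; a closed procedure keeps 5% familywise error per variable

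*Protocol article*

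**What the plan says.** The Statistical Analysis section of the protocol article sets the tests as follows: "An ANOVA or the Kruskal-Wallis test will be used for the analysis of the effects obtained in the phases one and two" of the study. It continues: "The Bonferroni correction for multiple comparisons will be employed as a" post-hoc test. For the first phase, "The fixed independent variables in Phase I will be group (congenital and acquired blindness, and sighted"), together with guide stick (with, without) and shoes (with, without). The threshold is P < "0.05 will be considered indicative of statistical significance". Neither the size of the Bonferroni family nor the sidedness of the Phase I tests is given.

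The first secondary objective in the Introduction is "to determine possible differences in PC" between the congenital and acquired groups. This is one of the three pairs to which the Bonferroni correction applies.

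**The concern.** Three groups give three pairs, so single-step Bonferroni tests each at 0.05/3 = 0.0167. The plan already has an omnibus test in front of these comparisons. With only three groups, that test is enough to allow each pair to be tested at the full 0.05 without exceeding 5% familywise error. The division by three therefore makes the pairwise tests stricter than 5% control requires.

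The cost falls on the contrast of scientific interest. If sighted people differ clearly from both blind groups, their two comparisons will be significant under either rule, and the correction mainly reduces the chance of detecting a real congenital-acquired difference. Phase I could miss a difference that the same data would have established within the same 5% familywise limit.

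**Working it through.** **Inputs from the article.** Three groups; omnibus ANOVA or Kruskal-Wallis; Bonferroni post hoc; threshold 0.05. 

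**Inputs that are assumptions.** Phase I states no sample size, effect, SD or power, so there is no figure of the plan's own to reproduce. The one power statement, "the sample size will be estimated with a unidirectional alpha of 0.05 and an 85% statistical power", sits in Sample Size Estimation, concerns the main trial and is not used here. Assumed: a family of three pairs, two-sided tests, normal data, 10 to 30 per group, and equal SDs except in step 4.

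**Step 1: why 5% per pair is enough.** The hypotheses are C = A, C = S and A = S. If any two hold, all three groups are equal. So only two kinds of null exist: all equal, or exactly one pair equal. An omnibus test at 5% covers the first, and a 5% test of the single equal pair covers the second. Claiming a pair only when both reject is a closed test with strong 5% control.

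**Step 2: loss by normal approximation, when the omnibus test always rejects.** Bonferroni power = Φ(1.960 + z_power − 2.394), where 1.960 and 2.394 are the two-sided critical values at 0.05 and 0.0167.
- Unadjusted power 50%: Φ(1.960 + 0 − 2.394) = Φ(−0.434) = 0.33, loss 16.8 points.
- 80%: Φ(1.960 + 0.842 − 2.394) = Φ(0.408) = 0.66, loss 14.2 points.
- 85%: loss 12.3 points. 90%: loss 9.8 points.

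**Step 3: simulation, 40,000 trials per setting, pooled-variance t tests.** Power on congenital versus acquired, true difference 0.8 SD:

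| n per group | Sighted 0.8 SD beyond acquired: Bonferroni → closed | Sighted midway: Bonferroni → closed |
|---|---|---|
| 15 | 39% → 57% | 39% → 44% |
| 20 | 53% → 70% | 53% → 58% |
| 30 | 74% → 87% | 74% → 78% |

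With the sighted mean equal to one blind group the gain is 9 to 11 points. When the effect is instead set to give 50%, 80% or 90% unadjusted power, the gain with sighted clearly apart is 17-18, 15-16 and 10-12 points. With sighted midway it is 3 to 5.

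**Step 4: familywise error per variable (200,000 runs, equal SDs).**
- All three equal: closed about 5.0%, Bonferroni about 4.3%.
- Only the two blind groups equal: closed 4.4% to 5.0%, Bonferroni about 1.7%.

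The result depends on the error term. If the sighted group is less variable and the pairwise tests use the SD pooled over all three groups, the closed rule's congenital-acquired error (n = 15 to 30) rises to 7.2-7.4% with a sighted SD 0.7 times that of the blind groups, and to 8.8-9.3% at 0.5 times. Bonferroni gives 2.8-2.9% and 3.7-3.9%. Using only the pair's own data brings the closed rule back to 5% at a cost of about 1 point of power.

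**The case against.** Bonferroni is standard and valid, and nothing in the section is misstated or uncontrolled. That stands: a reader might infer that the plan contains an error, and it does not.

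A reader might also take 12 to 18 points as the loss in this trial. The article does not support that, because it gives no Phase I size or effect, and the figure needs a sighted group clearly apart from both blind groups. The Discussion supports separation in part, citing poorer postural control in blind people. It also cites a study in which poor vision did not affect stability on a soft surface, and soft-surface stance is one of the stabilometry conditions. For some outcomes the gain may be only 3 to 5 points.

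Nor does Bonferroni buy nothing. When only the sighted group differs, it holds the congenital-acquired error near 1.7%, against up to 5% for the closed rule. Both are within the 5% limit for one variable, but the plan has many gait, COP and EMG variables. With 20 true-null variables (an assumed count), the expected false congenital-acquired claims are 20 × 0.0167 = 0.33 under Bonferroni and 20 × 0.05 = 1.0 under the closed rule. Neither rule controls error across variables.

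The design is not purely one-way. Guide stick and shoes give 2 × 2 = 4 conditions, so comparisons within conditions number up to 3 × 4 = 12. The three-group argument covers the group main effect only. It does not extend to the four groups of Phases II and III, where an omnibus gate followed by unadjusted pairs fails to control familywise error.

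Finally, the closed rule does not strictly contain ungated Bonferroni: in about 0.5% of runs at most, a pair passed Bonferroni although the omnibus test did not reject. This is too rare to matter.

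**Conclusion.** The point holds as an inexpensive improvement in efficiency. For the Phase I group main effect, a closed procedure keeps familywise error at 5% for each dependent variable and gains about 3 to 18 points of power on congenital versus acquired. Where in that range depends mainly on the sighted group:
- clearly apart from both blind groups: 12 to 18 points for a 0.8 SD difference with 15 to 30 per group;
- equal to one blind group: 9 to 11 points;
- midway between them: 3 to 5 points.

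The gain was positive in every setting examined. The figures rest on assumed group sizes and effects, normal data and a Bonferroni family of three. The 5% control also requires that the pairwise tests not borrow a pooled SD when group variances differ.

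**What to change.** In the Statistical Analysis section, replace the Bonferroni sentence with wording to this effect:

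- **Phase I, group main effect only.** If the omnibus group test (ANOVA, or Kruskal-Wallis where used) has P < 0.05, each of the three pairs is tested at two-sided 0.05 using only that pair's data: a Welch t test, or a rank test re-ranked within the pair after Kruskal-Wallis. If the omnibus test is not significant, no pair is claimed.
- **Comparisons within guide-stick or shoe conditions, and the four-group contrasts of Phases II and III.** Use Holm, with Shaffer's step where applicable, in place of Bonferroni. Do not use the omnibus-then-0.05 rule here.

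All three Phase I groups stay, and no extra participants are needed. The costs should be stated in the plan: simple simultaneous confidence intervals for the pairs are lost (unadjusted 95% intervals can be reported beside the tests); the congenital-acquired error is up to 5% rather than about 1.7% per variable when only the sighted group differs; and error is not controlled across the gait, COP and EMG variables, as is already the case under Bonferroni.

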## Materials and Methods

### Study Design

This study protocol is divided into three phases where phase 1 is a cross-sectional study to determine differences in postural control and gait between groups; phase 2 is a pilot study of phase three, a randomized, controlled, double-blind, clinical trial with blind individuals.

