### Sample and Recruitment

Preselected individuals will undergo a general assessment, with personal information, and anthropometric measurements which will be kept confidentiality under the responsibility of the researcher for the study.

The study will be conducted in three phases: (1) to determine differences in PC and gait between individuals with congenital and acquired blindness, and with/without a guide stick when wearing shoes and while barefoot compared to sighted people; (2) a pilot study to observe the effects of a cerebellar anodal tDCS on PC and gait during a proprioceptive exercises protocol; and (3) the exercise protocol with sample size calculation from phase 2. Figure 1 displays the flowchart of the proposed study process.

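### The Phase I model compares three non-randomised groups on group, guide stick and shoes only, leaving the between-group contrasts open to confounding by age, sex and height

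*Protocol article*

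**What the plan says.** The Study Design section states that "phase 1 is a cross-sectional study to determine differences in postural control and gait between groups". Under Sample and Recruitment, the two blindness groups are studied "with/without a guide stick when wearing shoes and while barefoot compared to sighted people". The first secondary objective in the Introduction, "1) to determine possible differences in PC", concerns congenital versus acquired blindness.

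The Statistical Analysis section writes the Phase I terms out: "The fixed independent variables in Phase I will be group (congenital and acquired blindness, and sighted"), and then "auxiliary resource (with and without guide stick), and shoes (with and without"). The tests are named as well: "An ANOVA or the Kruskal-Wallis test will be used for the analysis of the effects obtained in the phases one and two of the study". Bonferroni is the post-hoc correction. On outcomes it says: "The analyses will be performed considering spatiotemporal gait variables, variables of COP parameters, and EMG signals as the dependent variables".

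Three other places bear on the point:

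- Group Allocation assigns participants by envelope in Phases II and III only.
- The Abstract gives an age range of 18 to 55 years and both sexes for the blind participants. No age, sex or body-size criterion is given for the sighted participants.
- Sample and Recruitment says that preselected individuals undergo a "general assessment, with personal information, and anthropometric measurements". Body-size data should therefore exist, but no such variable is among the stated model terms.

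**The concern.** In Phase I the grouping factor is a characteristic that people bring with them, so nothing in the design balances the groups on other characteristics. The outcomes include velocity, step length, stride length and sway measures, which can reasonably be expected to vary with age and stature whatever the person's vision. If the groups differ in age, sex or height, the stated model assigns the resulting outcome difference to onset type or to blindness. The error can go either way: a difference that is not there, or a real one masked.

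At stake are the congenital-acquired contrast, which is secondary objective 1, and the blind-sighted contrasts. Phase I does not feed the sample size, which is to come from Phase II.

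**Working it through.** **No figure to reproduce.** The article gives no Phase I sample size, standard deviation, effect size or power. The first step is therefore a reading of the text, and the second is an illustration on stated assumptions.

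**Step 1: what could control for age, sex or height?**

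- Randomisation: Phases II and III only.
- Matching or frequency balancing of the groups: none described.
- Restriction: age 18 to 55 for blind participants, a span of 55 − 18 = 37 years. The eligibility criteria also exclude conditions, medication and symptoms that affect balance.
- Scaling of gait or sway variables to body size: none described.
- Model terms: group, stick and shoes. Kruskal-Wallis cannot carry a covariate, and ANOVA as listed has none.

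Only the restriction controls anything, and it does so partially.

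**Step 2: size of the bias.** Let r be the within-group correlation of a covariate with the outcome, and d the gap between groups in that covariate, in SD. With a linear relation and no true group effect, the spurious difference in outcome SD is

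b = r × d.

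Assumed range: r from 0.3 to 0.5 and d from 0.5 to 1.0. Neither is in the document.

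- Low: 0.3 × 0.5 = 0.15 SD
- Intermediate: 0.3 × 1.0 = 0.30 SD
- High: 0.5 × 1.0 = 0.50 SD

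The sample size does not enter this formula, so more participants do not shrink the bias.

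**Step 3: effect on the planned tests.** Assume n = 20 per group, one measurement per person, one group shifted by b, and within-group SD 1.

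Omnibus F test, three groups: degrees of freedom 2 and 3 × 20 − 3 = 57. The group means are 0, 0 and b, so the noncentrality is λ = n × (2/3) × b².

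Bonferroni pairwise test, assuming three comparisons: two-sided level 0.05/3 = 1.67%, pooled error with 57 degrees of freedom, noncentrality δ = b × √(n/2) = b × √10. It is treated as a stand-alone test.

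| Spurious difference b | λ | Omnibus F rejection (nominal 5%) | δ | Bonferroni pairwise rejection (nominal 1.67%) |
|---|---|---|---|---|
| 0.15 SD | 0.30 | 7.2% | 0.47 | 2.9% |
| 0.30 SD | 1.20 | 14.5% | 0.95 | 7.1% |
| 0.50 SD | 3.33 | 33.7% | 1.58 | 19.7% |

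**Step 4: sensitivity to sample size.** For the omnibus F at b = 0.15 SD, the rate is 6.0%, 7.2% and 8.4% with 10, 20 and 30 per group. At b = 0.50 SD it is 17.8%, 33.7% and 48.9%. With the bias held fixed, a larger study rejects more often.

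**The case against.** The strongest reply is that a journal article is condensed, and that matching or covariates may stand in a full protocol or SAP that is not shown. A list of fixed factors is also not where a continuous covariate would normally appear. This lowers confidence but does not dispose of the point. The article does not defer the Phase I model: it names the tests and lists the independent variables, and following it as written gives an unadjusted comparison.

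A second reply is that the imbalance is assumed. That is correct. A reader might infer from the list of admitted diagnoses, which mixes congenital and later-onset causes, that the acquired group will be older. The document gives no group ages or heights, and people with congenital blindness may be of any age in the range. An imbalance is possible, but it is not shown.

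A third reply concerns size. A reader might take the upper figure of about 34% as the error rate of the congenital-acquired comparison. Under the planned Bonferroni correction that rate is about 20%; the 34% belongs to the omnibus test. Both need the high correlation and the full 1 SD gap together. At the low end the omnibus rate is only a little above nominal.

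Finally, adjustment has limits of its own. Body mass may be a consequence of blindness, for example through lower activity, so adjusting for it could remove part of the effect under study. In congenital blindness, age and duration of blindness are the same quantity, so age adjustment cannot fully isolate onset type. Both objections stand, and they shape the remedy.

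**Conclusion.** The point holds as a defect of the stated Phase I analysis. Three non-randomised groups are compared by a model without any participant characteristic, and no matching is described. Any imbalance in age, sex or height passes directly into the between-group gait and centre-of-pressure contrasts, and multiplicity correction does not address it.

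The size of the actual bias is unknown. The illustrated 0.15 to 0.50 SD and the rejection rates that follow rest on assumed correlations, gaps and 20 per group, with a single covariate acting linearly.

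The scope is narrow. A reader might extend the criticism to the whole trial, but the documents do not support that. The stick and shoe contrasts appear to be made within the same people, so age, sex and height do not confound them. The tDCS comparison in Phases II and III is randomised. The point is worth correcting because the correction is cheap and concerns a named secondary objective; it does not threaten the main hypothesis.

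**What to change.** Analyse Phase I with a linear mixed model that keeps group, stick and shoes as stated, has a random effect for participant, and adds age, sex and height as prespecified covariates. Report the adjusted congenital-acquired and blind-sighted differences with 95% confidence intervals alongside the unadjusted ones. Use body mass only in a sensitivity analysis. Describe the adjusted congenital-acquired contrast as a comparison at equal age, since age and duration of blindness coincide in the congenital group.

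If recruitment of sighted participants is still open, matching them on age, sex and height would be a useful complement.

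The cost is a change of analysis wording and about three degrees of freedom, one each for age, sex and height. It needs no new assessment provided that height is among the anthropometric measurements already planned. Adjustment relies on the groups overlapping in age, so the age distribution by group should be reported. If overlap is poor, the adjusted contrast is an extrapolation and should be labelled as such.

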### Evaluation Procedures

All evaluations will be done at baseline and post-immediately therapeutic intervention, Also in 1 and 3 months as follow-ups (Figure 1).

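### The Phase II/III model makes the pre-intervention value an outcome level and lists no baseline covariate, so neither the group term nor group*time directly tests active against sham tDCS after treatment; the cost is efficiency and focus, not bias

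*Protocol article*

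**What the plan says.** The Introduction hypothesises that "tDCS can potentiate the effects of a proprioceptive exercises on both static and dynamic PC in blind subjects". That is a comparison of active with sham stimulation, on top of exercise, after treatment.

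Evaluation Procedures sets four visits: "All evaluations will be done at baseline and post-immediately therapeutic intervention, Also in 1 and 3 months as follow-ups".

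For Phases II and III, Statistical Analysis gives the independent variables: "for the fixed independent variables will be groups plus active and sham tDCS groups", then "evaluation time (preintervention, post-intervention, and follow-up" and the interaction of group with evaluation time. The pre-intervention measurement is therefore one level of the outcome. No baseline covariate is listed. The same section plans Bonferroni post-hoc comparisons and adds: "The effect size will be calculated based on the difference between means of the preintervention and post-intervention evaluations", with 95% confidence intervals.

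Sample Size Estimation states that in Phase II "participants will be randomly allocated into four groups (10 each group" and that Phase III is to be sized from the resulting analysis of variance.

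**The concern.** A factorial model with baseline as a time level offers two terms that involve treatment, and neither matches the hypothesis.

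- **Group term.** Its null is no difference averaged over all visits, including the one before treatment. Randomisation makes the true difference at that visit zero, so including it dilutes the effect.
- **Group*time.** Its null is parallel profiles over all visits. Power is spread over patterns the hypothesis does not concern, such as different decay between 1 and 3 months. A significant result does not by itself show that active is better than sham at the end of treatment.

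Baseline is measured in everyone, but the model does not use it to reduce the error of the post-treatment comparison. At stake are a real tDCS effect that is harder to detect in Phase II, and more participants than needed in Phase III, which is sized from the same kind of analysis.

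**Working it through.** The article states no detectable difference, SD, correlation or final sample size, so there is no figure of its own to reproduce.

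**Inputs from the article.** Four arms of 10, hence n = 20 active and 20 sham; four visits; significance at 0.05.

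**Assumptions.** Two-sided test; SD 1; equal correlation r between visits; a tDCS effect d that is the same in both exercise types. Active against sham is taken as a two-level factor, the milder reading of the group wording. Error degrees of freedom are 40 − 4 = 36, or 35 with a covariate.

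**Dilution.** For a sustained effect (0, d, d, d) the mean over visits is 3d/4. If follow-up counts as one level it is 2d/3.

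**Formulas for a sustained effect, evaluated at d = 0.6, r = 0.5.**

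1. Group term: noncentrality 0.75d / √[(2/n)(1+3r)/4] = 0.45 / √(0.1 × 0.625) = 1.80. Power 42%.
2. Group*time: λ = (n/2) × 0.75d² / (1−r) = 10 × 0.27 / 0.5 = 5.4 on 3 and 108 df. Power 46%.
3. Post mean minus baseline, 1 df: variance (1+2r)/3 + 1 − 2r = 0.667; 0.6 / √(0.1 × 0.667) = 2.32. Power 62%.
4. ANCOVA, immediate post visit: variance 1 − r² = 0.75; 0.6 / √(0.1 × 0.75) = 2.19. Power 57%.
5. ANCOVA, mean of post visits: variance (1+2r)/3 − r² = 0.417; 0.6 / √(0.1 × 0.417) = 2.94. Power 82%.

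**Power, sustained effect.**

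| d, r | Group | Group*time | Change, post mean | ANCOVA, immediate post | ANCOVA, post mean |
|---|---|---|---|---|---|
| 0.5, 0.5 | 31% | 33% | 47% | 43% | 66% |
| 0.5, 0.7 | 26% | 52% | 68% | 58% | 79% |
| 0.6, 0.5 | 42% | 46% | 62% | 57% | 82% |
| 0.6, 0.7 | 35% | 69% | 83% | 73% | 91% |

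**Splitting the gap.** The change and ANCOVA tests on the post mean both have 1 df and differ only in how baseline is used. That difference is about 8 points (0.6, 0.7) to 20 points (0.6, 0.5). The rest of the gap from group*time to ANCOVA on the post mean is the step from group*time to the 1-df change test, about 14 to 16 points. It comes from the omnibus form.

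**Fading effect (full, half, none).** At d = 0.5, r = 0.5 the visit effects are 0, 0.5, 0.25, 0, with mean 0.1875.

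- Group*time: the squared deviations sum to 0.3125 − 4 × 0.1875² = 0.172; λ = 10 × 0.172 / 0.5 = 3.44.
- ANCOVA, post mean: the effect is 0.25, so noncentrality is 0.25 / √(0.1 × 0.417) = 1.22.

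| d, r | Group | Group*time | ANCOVA, immediate post | ANCOVA, post mean |
|---|---|---|---|---|
| 0.5, 0.5 | 11% | 30% | 43% | 22% |
| 0.5, 0.7 | 10% | 48% | 58% | 28% |

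**Sample size.** For 85% power at d = 0.5, sustained, two-sided, with the formulas above solved for n: group*time needs 34 per arm at r = 0.5 and 21 at r = 0.7. ANCOVA at the immediate post visit needs 28 and 19.

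**The case against.** **The planned method is valid and conventional.** Group*time is the usual test of differential change in a pre/post design. Under randomisation its type I error is kept, and so is that of the group term. This stands. A reader might infer that having baseline among the outcome levels biases the comparison; nothing in the article supports that. A longitudinal model that constrains baseline means to be equal also keeps baseline as an outcome, with efficiency close to ANCOVA. The article does not describe such a constraint.

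**The gain depends on the comparator.** This also stands. Against ANCOVA at the immediate post visit, group*time loses only about 4 to 11 points in the sustained cases tabulated. At r = 0.8 the two are about equal, and at r = 0.9 group*time is slightly ahead (96% against 94% at 0.5 SD). The larger gaps come from averaging three visits under an assumed constant effect.

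**Nobody need read the group term as the treatment test.** The article does not say that it is, and it lists the interaction explicitly. The large group-term loss therefore matters only if that term is used for the tDCS conclusion.

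**Post-hoc tests and pre-to-post effect sizes are planned.** They are, but no active-against-sham contrast or visit is named for them, and they are not described as adjusted for baseline.

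**Such detail belongs in an analysis plan.** An unseen plan could add contrasts. The article, however, does not merely leave baseline handling open. It makes the pre-intervention value a level of the time factor, and a baseline covariate would require changing that factor.

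**Conclusion.** The point holds as a matter of efficiency and focus. The stated terms do not directly test the tDCS hypothesis, and baseline is not used to sharpen the post-treatment comparison. With 20 per side, equal correlation of 0.5 to 0.7 and a sustained effect of 0.5 to 0.6 SD, the power attributable to baseline handling alone is about 8 to 20 points. The further gap to group*time comes from its several degrees of freedom. Effect size, correlation pattern and persistence are all assumed, and the loss for group*time disappears as the correlation rises.

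Three stronger readings go too far:

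- **That the whole shortfall is due to baseline being an outcome level.** The two 1-df tests show otherwise.
- **That any baseline-adjusted test does better.** With a fading effect, ANCOVA on the post mean has 22% power against 30% for group*time at 0.5 SD and r = 0.5.
- **That Phase III will be underpowered.** It is to be sized for 85% power from Phase II analysis of variance results, so the likelier cost of an inefficient test there is extra participants.

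**What to change.** In Phases II and III, remove the pre-intervention value from the levels of evaluation time and enter it as a covariate, by ANCOVA or by a mixed model on the post-treatment visits. State that the tDCS conclusion rests on the baseline-adjusted active-minus-sham contrast at the immediate post-intervention visit. Report the 1-month and 3-month contrasts as secondary tests of whether the effect lasts. Base the Phase III sample size on the same contrast.

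The cost is wording and one degree of freedom; baseline is already collected. There is a trade-off: one visit must be named in advance, and if the effect is sustained, the immediate post visit gives up power against the mean of the post visits (57% against 82% at 0.6 SD, r = 0.5). In return, the test keeps its power if the effect fades.
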